## Abstract

**Background:**

Informed consent is among the biggest challenges in recruiting participants for clinical research studies. Researchers face many challenges in conducting clinical trials, some of which include budgetary restrictions, lack of trained personnel, and difficulty recruiting study participants—particularly minorities and participants from rural communities.

**Objective:**

The objective of this study is to utilize telemedicine to improve the informed consent process for clinical trials and studies. We aim to assess the feasibility and efficacy of the teleconsent intervention among residents in urban and rural settings.

**Methods:**

This study will be conducted separately yet concurrently at two institutions, the Medical University of South Carolina and the University of North Carolina at Chapel Hill, to compare results within and across institutions.

**Results:**

Enrollment for Phase 1 began in March of 2018 and concluded in May 2018. Data transcription and analysis will be conducted through June and September of 2018.

**Conclusions:**

In this paper, we present a novel approach for conducting informed consent using a new telemedicine modality, namely, teleconsent. Teleconsent presents the ability to conduct a live interaction among clinical research coordinators and potential participants while synchronously presenting the consent form on the screen and obtaining participant’s signature through doxy.me, the teleconsent system. Teleconsent provides potential to improve obtaining informed consent from potential clinical trial participants.

**Registered Report Identifier:**

RR1-10.2196/11239

## Introduction

### Challenges Obtaining Consent for Research

Researchers face many challenges in conducting clinical trials, some of which include budgetary restrictions, lack of trained personnel, and difficulty recruiting study participants—particularly underserved and participants from rural communities [1]. Failure to meet enrollment goals can lead to a considerable amount of research waste, including costly time extensions [2,3], underpowered study results, and unpublished results as well as study termination and costing research institutions and sponsors a substantial investment in both money and time every year. Moreover, an ongoing concern in clinical trials is the typical underrepresentation of underserved individuals of a population [4], some of whom may lack the means for transportation to the study site but may have access to mobile devices, smartphones, or community centers (eg, public libraries or coffee shops) where the internet and computers are available [5]. This underrepresentation of underserved individuals could hinder the generalizability of study results and the translation of knowledge and potentially life-saving interventions into the routine clinical practice [4,6-9]; therefore, innovative approaches to increase access, improve participants’ experience, and increase trust to research studies are needed [10-12].

Multisite and offsite clinical trials often impose considerable travel costs and time commitments on participants [13]. The consenting process is often performed in-person with participants visiting with study personnel before, during, or after their clinical visit. In multisite clinical trials, consent often requires faxing or mailing of documents to the coordinating site [12]. In addition, training of clinic staff to maintain the regulatory compliance can add to the burden of study participation. Finally, as direct-to-patient recruitment sites and other nontraditional, novel recruitment approaches increase in popularity [14], the current informed consent process will be difficult, if not impossible, to scale. Informed consent readability and comprehension continue to be a major issue; a participant’s understanding during the consent process cannot easily be assessed by telephone or obtaining consent through an Web-based form [15,16]. The growing complexity of clinical studies and trials and the need to integrate trials into routine care (ie, the national movement toward more pragmatic clinical trials supported by the National Institutes of Health and the Patient-Centered Outcomes Research Institute, in particular) demand more accessible solutions for eliciting consent [17].

### Teleconsent as a Solution

The Biomedical Informatics team at the Medical University of South Carolina (MUSC) has developed “teleconsent,” an innovative, informed consent approach that leverages telemedicine technology to conduct remote, live consent sessions between participants and researchers. Teleconsent allows research personnel to meet and discuss the study with a prospective participant virtually using a video feed, share an informed consent document that can be collaboratively filled out by a participant and study personnel in real time, and generate an electronically signed informed consent document (Figure 1) available for immediate PDF download or print by both parties. This process can eliminate the inefficiencies related to travel, time, and management of personnel at remote sites [18]. In addition, the addition of a telehealth session will provide visual cues that may help research staff evaluate a potential participant’s understanding of risks, benefits, and other important elements of consent. New e-consent technologies may overcome some of the challenges related to comprehension by adding multimedia and interactive sessions testing participants’ comprehension [19]. To these tools, teleconsent adds opportunities for enhanced communication and remote access. Preliminary results, pilot studies, and anecdotal feedback regarding teleconsent have shown that participants are generally highly satisfied with teleconsent and did not experience difficulties understanding and navigating teleconsent and the process itself; however, there was a moderate, inverse relationship between age and satisfaction [20].

**Figure 1 figure1:**
[figure not shown]
A mock consent form displayed in the Doxy.me software during a live teleconsent session.

### Need for This Research

We are conducting a study that evaluates participants’ reactions to the teleconsent software, including their feelings regarding privacy and ease of use. We have 3 main objectives. First, we seek to understand the feasibility of using telehealth in rural areas, acceptability among underserved populations, and ethical and privacy concerns of using the teleconsent software and remote communication through participant interviews, particularly among minorities, rural, and elderly participants aged >65 years. Second, we aim to evaluate the quality of informed consent by comparing participants’ perception and comprehension using either teleconsent or paper-based consenting in ongoing clinical studies, through partnerships with investigators conducting those studies, by assigning participants to either teleconsent or traditional paper-based consenting. In addition, we will determine to what extent, if any, the teleconsent process affects participants’ informed consent and the workflow of research staff conducting the studies. Third, we intend to assess the workload on research assistants and their perception of the usability of teleconsent in terms of ease of use and user friendliness of the interface.

## Methods

### Study Setting

Study procedures will be conducted concurrently at 2 institutions, the MUSC and the University of North Carolina at Chapel Hill (UNC) to compare results both within and across institutions.

### Study Overview

This study is divided into 2 phases, to be completed in subsequent order and concurrently at both study sites. Phase 1 aims at meeting the first objective by conducting remote mock consent sessions using the Doxy.me software (Figures 1 and 2) and through interviewing participants about their experiences, preferences, and concerns with the technology, processes, and privacy.

In the second phase, we will complete our second and third objectives by partnering with ongoing clinical trials and assigning participants to either teleconsent or traditional paper-based consenting and then assessing the quality of informed consent and workload, among other metrics; of note, this part of the study will be initiated in the winter of 2019. Full procedures for both study parts are outlined in the “Procedures” section of this paper.

### Eligibility Criteria

For phase 1, prospective participants are required to be, at least, 18 years of age, currently residing in North or South Carolina, speak English as their first language, and have access to the internet and a computer with a microphone and camera. Any participant who does not meet the inclusion criteria will be excluded from the study. Our decision to exclude participants who do not reside in North Carolina is because one goal of this software is to study how North Carolina residents react to the software and compare the data to that of our MUSC. In addition, we choose to exclude participants who do not speak English as their first language to control for potential language barriers in this feasibility study. Moreover, the technological requirements of Doxy.me require participants to have access to a laptop or desktop with the appropriate audio-video capabilities; notably, the software was not compatible with tablets, such as iPads, or smartphone at the time of this publication. For phase 2, the eligibility criteria for our study is the same as those for the clinical trial sites.

### Recruitment

Each study site will have a unique recruitment process. For phase 1, in South Carolina, participants will be recruited through the dissemination of Institutional Review Board flyers placed in clinical and community settings and distributed by our Community Advisory Board members, advertisements, word-of-mouth, and at community-based clinic sites. Participants at UNC will be recruited through a researcher-participant networking website called Join the Conquest, word-of-mouth, and direct participant recruitment at Broad Street Clinic in Morehead, North Carolina. In addition, participants’ recruitment at UNC will be facilitated by 2 research assistants, the principle investigator and coprinciple investigator, and the staff at Broad Street Clinic. At MUSC, recruitment will be facilitated by the research coordinator. Both institutions will implement a prescreening eligibility questionnaire. On Join the Conquest, persons interested in the study will be directed to a Qualtrics eligibility survey, which will include demographic information. At MUSC, surveys will be completed through the Research Electronic Data Capture Platform (REDCap) [21]. From the pool of prospective participants obtained, we will select a total of 40 through a screening process that will be detailed later. Chosen participants will be offered gift cards or cash as remuneration.

**Figure 2 figure2:**
[figure not shown]
The teleconsent software allows the research coordinator and participant to sign the consent form in real time electronically.

For phase 2, participants will not be directly recruited for our study. Instead, we will partner with investigators conducting ongoing clinical research and assign those study participants to use either teleconsent or traditional paper-based consenting for the informed consent process. In total, 64 patients and up to 10 research assistants will be involved in this part of the study at the UNC site, though the number of research assistants may be as low as 2. Patients will be paid each time a set of surveys are completed. Research assistants will be paid upon the completion of each National Aeronautics and Space Administration (NASA)-Task Load Assessment (TLX) form (to be completed after each consent session) and also upon the completion of each System Usability Scale (SUS; to be completed approximately 3 times throughout the study). In addition, research assistants will be paid for participation in a focus group.

### Screening

For phase 1, participants’ screening will occur through the Qualtrics or REDCap surveys or over the phone. The demographic information collected during the screening process (age, gender, race, ethnicity, and county) will be used to select a group of participants who are coming from a variety of backgrounds to study potential differences between reactions to teleconsent among various demographic groups. For phase 2, participant screening will not occur.

### Randomization

No randomization will be involved in phase 1. For phase 2, if the parent study permits, participants will be either randomly assigned to each of teleconsent or traditional consent. When random assignment is not possible, for example, in studies in which some participants do not have the option of being assigned to traditional consent, thereby negating random assignment, we will use the propensity score matching after assignment to either teleconsent or traditional consent. Once verbally consented through one of these means, participants will undergo the informed consent process.

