### Data Analysis

In phase 1, all interviews will be professionally transcribed and imported into the NVivo 12.0 (QSR International Pty, Doncaster, VIC, Australia) qualitative analysis software. Verification of the transcript accuracy will be performed prior to analyzing the text. An iterative process will be used in the analysis of the data. Then, 2 team members will code the data following its transcription by tagging segments of text in the transcripts to a concept, expanding, refining, and reducing the concepts, and discussing the findings in detail to allow for cross-validation of findings between the 2 sites [28]. A coinvestigator at MUSC with advanced training in research ethics and bioethics will explore the ethical appropriateness and associated principles of teleconsent using an integrative bioethical approach, and the MUSC research team will review emerging findings at the midpoint and conclusion of coding to consider what additional data will be necessary to refine our understanding of the participants’ perspectives related to teleconsent and determine overall themes. In addition, any feedback about the Doxy.me software will be submitted to developers at MUSC.

In phase 2, for patient participants, descriptive statistics (means, SDs, medians, etc) of responses to the survey instruments will be used to characterize the 2 groups (ie, teleconsent vs paper-based consent). Participants will be stratified with respect to demographics and clinical study. Each of the survey instrument summary scores and subscale scores will be essentially continuous variables; as such, comparisons between groups will be delineated through analysis of covariance modeling. In these models, the instrument score will serve as the dependent variable, with the experimental group serving as the key independent variable of interest. The analysis of covariance model includes participant factors, such as education and other demographics, as covariates in the models.

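### Propensity score matching cannot supply a paper-consent comparator for participants who had no paper option, and the rule gives up randomization for others in the same parent study who could have had it

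*Protocol article*

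**What the plan says.** For phase 2, the Randomization section sets random assignment as the default: "if the parent study permits, participants will be either randomly assigned to each of teleconsent or traditional consent". The fallback opens with "When random assignment is not possible, for example, in studies in which some participants do not have the option", and for those studies the remedy is matching after assignment: "some participants do not have the option of being assigned to traditional consent, thereby negating random assignment, we will use the propensity score matching".

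The Procedure section fixes 32 teleconsent and 32 paper participants per site. It states that 64 per site, 128 in total, give 80% power for effect sizes of about 0.50.

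The Data Analysis section describes one model for patient participants: "comparisons between groups will be delineated through analysis of covariance modeling", "with the experimental group serving as the key independent variable of interest". The covariates named are education and other demographics. The section also says that participants are stratified by demographics and by clinical study. It names no term for how a participant was assigned, no restriction to people who could have had either mode, and no separate analysis of randomized participants.

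**The concern.** Matching on a propensity score estimates an effect only where each person had some chance of either treatment. In the article's example, part of the study population had no chance of paper consent. The defect is in the rule itself: whichever matching variables or caliper a full analysis plan may set, they cannot create a counterpart who does not exist.

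The trigger is also wider than it needs to be. That some participants lack the paper option is taken to rule out random assignment in that study, yet the rest of its participants could still be randomized. This can be put right only before assignment.

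At stake is the phase 2 comparison of consent quality. The reason for having no paper option could be distance or transport, which may be related to comprehension scores. The Introduction notes that underserved people may lack transport to the study site, and the Study Instruments section links lower education and advanced age to lower comprehension. The Discussion hypothesizes no significant difference in consent quality, so lost power, or a bias that masks a difference, would favour the expected conclusion.

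**Working it through.** **1. The plan's own power figure.** Inputs from the Procedure section: 64 per arm over both sites, effect size d = 0.50. Two-sided alpha of 0.05 is stated in Data Analysis for study personnel and is assumed here for patients.

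Noncentrality = d × √(n₁n₂/(n₁+n₂)) = 0.50 × √(64 × 64/128) = 0.50 × √32 = 2.83. The normal approximation gives Φ(2.83 − 1.96) = 80.7%, and the noncentral t gives 80.1%. The figure reproduces, but only with both sites pooled and all 128 analysed; 32 versus 32 gives 50.4%. The t test requires 63.8 per arm, so there is no slack.

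**2. What matching can do for a participant with no paper option.** P(paper) = 0, so the true propensity for teleconsent is 1. Two outcomes are possible, and for any one such participant they are alternatives:

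- The propensity model captures the reason. The participant goes unmatched and is lost, which costs power but adds no bias on that person's account.
- The model misses the reason. The participant is matched to someone who differs on it, which keeps the numbers but leaves possible bias.

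**3. First outcome: lost numbers.** The share lost is an assumption, and so is one-to-one matching, since the article states no ratio. Two-sided t test, d = 0.50:

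| Teleconsent arm unmatched | n per arm | Power |
|---|---|---|
| 0% | 64 | 80.1% |
| 10% | 58 | 76.1% |
| 20% | 51 | 70.6% |
| 30% | 45 | 65.0% |

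If all 64 paper participants were kept against 51 teleconsent participants, the noncentrality would be 0.50 × √(51 × 64/115) = 2.66 and power 75.2%. A different matching ratio therefore softens the loss but does not remove it.

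**4. Second outcome: retained but unlike.** Everything here is assumed. Let q be the share of the 128 from a non-randomized study, g the share of those with no paper option, and δ their difference in score (in SD) for reasons not adjusted for. Everyone else splits 50:50 and the true effect is zero. No-paper participants are all in the teleconsent arm, where they make up 2qg/(1 + qg), so the bias is δ × 2qg/(1 + qg).

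- Low end, q = 0.5, g = 0.2, δ = 0.3: 0.3 × 0.2/1.1 = 0.055 SD.
- High end, q = 1, g = 0.4, δ = 0.5: 0.5 × 0.8/1.4 = 0.286 SD.

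A simulation of 4,000 trials per scenario gave 0.05 to 0.28 SD, with type I error from 5.5% to about 30%. Adding a term for parent study helped only slightly: with q = 0.5, g = 0.4 and δ = 0.5, the bias fell from 0.16 to 0.13 SD. That is as expected, because a study term does not create overlap within a study. These figures show how the mechanism behaves; they are not an estimate for this trial.

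**The case against.** The best reply is that the text claims less than a critic might suppose.

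- A reader might infer that matching is prescribed exactly where it fails. The no-paper case is introduced as an example and concerns some participants. Matching can still work for others in that study who could have had either mode, and in other non-randomized settings. This stands.
- A reader might infer that matched and randomized participants are pooled. That is never stated. It is an inference from the single model description, and stratification by clinical study would partly separate the two kinds of evidence, since permission to randomize is set by parent study. This also stands, although stratification does not repair missing overlap within a study.
- A reader might conclude that the teleconsent effect is confounded. Randomization is the default, only two candidate trials are named, and nothing shows that either prevents it. Confounding is a conditional risk. Education is already a covariate, and the matching variables are not stated, so they cannot be called inadequate.
- A reader might add the mirror problem. Phase 2 follows the parent trials' criteria, and "For phase 2, participant screening will not occur", while "the software was not compatible with tablets, such as iPads, or smartphone at the time of this publication", so people without a computer might be assigned to teleconsent. The incompatibility is described among the phase 1 criteria as of publication, phase 2 starts later, and the partner sites have amended their ethics protocols to include teleconsent. The documents do not show that feasibility goes unchecked there.

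What survives is the core: no matching specification gives a no-paper participant a valid comparator, and the rule does not confine randomization or comparison to those eligible for both modes.

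**Conclusion.** The concern holds in a limited, conditional form. If a parent study does not allow all its participants to be randomized, following the stated rule yields either fewer than the 64 versus 64 that the 80% power requires or a contrast open to confounding by the reason for assignment. It also forgoes randomization that was available for part of that study. An assumed 20% loss under one-to-one matching brings power to about 71%. The direction and size of any bias are unknown, and the 0.05 to 0.28 SD range rests wholly on assumed inputs. If every parent study permits full randomization, the problem does not arise. The documents do not support saying that the phase 2 estimate is confounded or that matched and randomized data will be pooled.

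**What to change.** Before phase 2 assignment begins:

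1. Record for each participant, before assignment, whether paper consent and teleconsent are each feasible.
2. Where the parent study permits, randomize everyone for whom both are feasible, even if others in that study have only one mode.
3. Make the randomized comparison, analysed as assigned, primary.
4. Restrict any propensity-based comparison to participants eligible for both modes, and report it as a separate supportive analysis. Matching can be kept for this.
5. Describe single-mode participants separately.

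The direct cost is two checklist items and revised analysis wording. The real cost is scope: the main comparison covers only people able to use either mode, which may leave out some of the remote participants teleconsent is meant to reach, and enrolment may be slower. Randomization still depends on the parent investigators' permission. With two candidate trials, the randomized set could be small, so the number expected should be checked with the partner studies and the power statement tied to it.

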### Procedure

In phase 1, following the initial eligibility screening and identification as possible participants, interested individuals will be contacted by emails or phone to invite them to schedule a 1-hour mock consent session with a member of the study team. Before the mock consent session, participants at UNC will e-sign an Web-based consent form sent by Qualtrics and those at MUSC provide verbal consent at the time of scheduling, which is confirmed by the coinvestigator prior to participating in study procedures. During the mock consent session, study personnel will give participants a brief overview of Doxy.me and teleconsent before walking participants through a mock consent form created for this study. The purpose of the mock consent form is not to actually complete an informed consent session but to highlight the functionalities of the software. Immediately after the completion of the mock consent process, study personnel will conduct audiorecorded, semistructured interviews with participants about their experiences. After the study completion, participants will either receive cash or a gift card sent electronically or mailed to their residence(s). In total, 40 participants are to complete phase 1 of the study at each site, for a total of 80 participants between UNC and MUSC.

For phase 2, participants (n=64 at each site) will be assigned to either consenting for the clinical trial through teleconsent (n=32) or through paper-based consenting (n=32). Notably, 64 subjects per site (totaling n=128 between sites) will provide 80% power to detect modest differences (effect sizes ~0.50) between groups with respect to the survey instrument scores. After consenting for participation in the teleconsent study, participants will undergo the informed consent process using either teleconsent or traditional consent. After the completion of the consent process, participants will immediately fill out the quality of informed consent (QuIC), Decision-Making Control Instrument (DMCI, and Short Assessment of Health Literacy-English version (SAHL-E). Thirty days postconsent, participants will be asked to fill out this set of surveys once more electronically; they will be paid for each set of surveys completed.

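### Phase 2 appears to assign the consent mode before asking people to join the teleconsent study, so refusal can depend on the arm and bias even the randomised comparison

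*Protocol article*

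**What the plan says.** Four places in the protocol article bear on the order of events in phase 2.

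- **Recruitment.** Participants are not recruited directly. The investigators partner with ongoing studies and "assign those study participants to use either teleconsent or traditional paper-based consenting for the informed consent process". No step for consent to the teleconsent study is mentioned.
- **Randomization, assignment.** Two routes are given: "if the parent study permits, participants will be either randomly assigned to each of teleconsent or traditional consent", and otherwise "we will use the propensity score matching after assignment to either teleconsent or traditional consent".
- **Randomization, consent.** The next sentence reads "Once verbally consented through one of these means, participants will undergo the informed consent process".
- **Procedure.** At each site participants are "assigned to either consenting for the clinical trial through teleconsent (n=32) or through paper-based consenting (n=32"). After a sentence on power, the text continues: "After consenting for participation in the teleconsent study, participants will undergo the informed consent process using either teleconsent or traditional consent". Then: "After the completion of the consent process, participants will immediately fill out the quality of informed consent (QuIC"), together with the other surveys, which are repeated at 30 days.

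The Data Analysis section plans an analysis of covariance for each instrument score, with education and other demographics as covariates.

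**The concern.** Random assignment protects a comparison only if what happens between assignment and outcome measurement does not sort people differently in the two arms. If agreement to take part is sought once the mode is known, some people may decline because of the mode. The QuIC and DMCI are completed only after the consent session, so those people leave no outcome. The analysed groups are then the assigned groups minus whoever disliked the assignment.

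The two modes plausibly provoke different refusals, since one needs video and a computer and the other needs paper and usually attendance. If the people lost from one arm would also have scored differently, the difference in means is shifted. This matters particularly here because the Discussion expects no significant difference in consent quality. A shift that offsets a true deficit would look like confirmation. Propensity score matching is planned only for the non-randomised route, and matching on measured covariates would not remove selection on unmeasured willingness to join.

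**Working it through.** **1. Order of events.** In the Randomization section, the only consent means named just before the verbal-consent sentence are teleconsent and traditional consent. The natural reading is therefore: assign the mode, obtain verbal consent through that mode, then run the parent-trial consent. The Procedure section fixes study consent before the parent-trial consent process, but does not say whether it comes before or after assignment. The Recruitment section gives no order. No section states that study consent precedes assignment or disclosure.

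**2. The plan's own figure.** The Procedure section states that "64 subjects per site (totaling n=128 between sites) will provide 80% power to detect modest differences (effect sizes ~0.50"). With 64 per arm pooled over sites, a difference of 0.50 SD and two-sided alpha .05, t-test power is 0.801, so the 80% reproduces for the pooled 128. Alpha and sidedness are stated in the study-personnel paragraph of Data Analysis and are assumed to apply to participants. The order of consent does not change this figure; it affects what the 64 versus 64 comparison estimates.

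**3. Illustrative shift.** Refusal rates and decliners' scores are assumptions, because the documents give neither. Let a fraction p of one arm decline with no matching refusal in the other, and let decliners score s SD below those retained. If those retained average r, the whole arm averages

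(1 − p)·r + p·(r − s) = r − p·s,

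so the retained mean exceeds the whole-arm mean by **p·s**. With 64 analysed per arm and unit SD, the noncentrality is p·s / √(2/64) = p·s / 0.1768. The last column supposes that the arm losing its low scorers is truly 0.50 SD worse, so that a difference of 0.50 − p·s is left to detect.

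| p | s | Shift p·s (SD) | Share of 0.50 | Noncentrality | Rejection rate, no true difference | Power if that arm is truly 0.50 SD worse |
|---|---|---|---|---|---|---|
| 10% | 0.5 | 0.05 | 10% | 0.28 | 5.9% | 71% |
| 20% | 0.8 | 0.16 | 32% | 0.91 | 14.6% | 48% |
| 25% | 0.8 | 0.20 | 40% | 1.13 | 20.2% | 39% |

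**4. Refusal in both arms.** As a second illustration, let willingness to join be normal and correlated ρ with the outcome in both arms. If a fraction q declines, the retained mean shifts by ρ·φ(z_q)/(1 − q), where φ is the standard normal density and z_q its q-quantile. The bias is the difference between the two arms' shifts (normal approximation, 64 per arm).

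- Refusal 10% in both arms: bias 0, type I error 5%.
- Refusal 10% versus 30%: bias 0.06, 0.09 or 0.15 SD for ρ = 0.2, 0.3 or 0.5; type I error 6.3%, 8.1% or 13.7%.

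In this model there is no bias unless refusal differs by arm and is related to the outcome.

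**The case against.** **The order rests on one loose sentence.** The means referred to could be the two assignment routes rather than the two consent modes, and neither the Procedure nor the Recruitment section corroborates the sequence. This stands as a limit on how firmly the order can be asserted. It does not remove the point: if consent is meant to come first, the Randomization section misstates it; if assignment comes first, the design is exposed.

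**Planned adjustment helps.** Analysis of covariance on education and demographics would absorb selection acting through those factors. That is correct, and the figures above are unadjusted. Selection through unmeasured willingness or comfort with the technology would remain.

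**The direction is open.** A reader might infer that teleconsent refusers will be older, low-scoring people, so that teleconsent is bound to look too good. The documents do not support that. The inverse relation between age and satisfaction, in the section on teleconsent as a solution, concerns people who had used teleconsent, not refusers. The same sentence reports high satisfaction and no difficulty with understanding or navigation. The Introduction's account of travel and time burdens could equally drive refusal in the paper arm.

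**The remedy is incomplete.** Consenting first does not stop someone withdrawing once the mode is revealed. In parent studies with no traditional option for some participants, the mode may be evident beforehand. Both points stand and limit the fix.

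**Conclusion.** The concern holds as a risk created by the sequence as written. The natural reading puts study consent after assignment, apparently in the assigned mode, and no text places it earlier. Arm-dependent refusal before any outcome is therefore possible, including where assignment is random, and covariate adjustment would remove only part of its effect.

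A reader might go further and conclude that the phase 2 comparison is self-selected or that randomisation has failed. The documents do not show that: it would need refusal that differs by arm and is related to the outcome, and no rates are given. Under the assumptions used, the effect runs from negligible (0.05 SD, about 6% rejection) to material (0.20 SD, about 20% rejection, 40% of the difference the study is sized for). The larger values need one-sided refusal of 20% to 25% and a gap of 0.8 SD. The stated 80% power for the pooled sample is not in question here.

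**What to change.** Reconcile the Randomization and Procedure sections into one explicit sequence:

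1. Take verbal consent to the teleconsent study from each parent-trial candidate by one identical route, before the mode is assigned or disclosed. In non-randomised parent studies, do this where feasible.
2. Assign the mode.
3. Run the parent-trial consent in that mode and collect the surveys.
4. Analyse by assigned arm, and report refusals and withdrawals after assignment separately by arm.

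The cost is a small protocol change and an IRB modification; the verbal consent already planned simply moves one step earlier. The Timeline has phase 2 starting in January 2019, so the change should be in place before the first assignment. Some people may agree to the study and then withdraw on learning their mode. The change does not prevent this, and it cannot supply the missing surveys. It does make the losses visible by arm, so that their possible effect can be judged.
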